In total, 160 participants will be recruited from CPRD using an algorithm containing validated COPD diagnostic codes. Patients with data in CPRD who have a diagnosis of COPD based on a validated code list by Quint *et al*^21^ are not coded for mild COPD (ie, moderate or severe patients only), are not coded as a current smoker, are aged >35 years, and have had between one and two identified exacerbations in the preceding year will be included. After running the algorithm to identify suitable participants, general practices that have agreed to participate in research through CPRD will be sent a list of the potential participants. GPs will confirm to CPRD the suitable patients identified previously using the Vision Identification. CPRD will then send participant information packs to the general practices to disseminate to the potential recruits. The information pack will contain a cover letter from the general practitioner introducing the study, a participant information sheet with detailed information of what the project entails, and an expression of interest form that participants can complete and send to the research team in a prepaid envelope. Once received, the research team will then be able to contact the participant to enrol them in the study through a clinic appointment. Participants will also be recruited from respiratory clinics in secondary care as an additional recruitment option.

The sample size of 160 patients is based on the estimated number of exacerbations for the cohort. Since we will recruit with a bias towards patients with COPD with a history of COPD exacerbations, we have made the conservative estimate that we will capture at least 200 exacerbations with a cohort of 160 patients. We have calculated a minimum detectable relative risk (RR) to detect associations at p<0.05 with 80% power. With 200 exacerbations, this will permit detection of about RR=1.65 in the highest 20% of days compared with others (RR=2.00 in the highest 10%). Other more common outcomes and in particular peak flow will have power to detect smaller associations.^22^

Two secondary recruitment methods will be established to make up any shortfall in recruits through the CPRD: recruitment from respiratory clinics in local hospitals and presentations at British Lung Foundation ‘Breathe Easy’ respiratory disease support groups.

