#### Monitoring phase

At the clinic, participants will be provided with a PAM and instructed to keep the monitor at home and take it out with them for a minimum of once a week for up to 6 months. An initial questionnaire will collect information on lifestyle factors and residence characteristics, such as type of cooker used in the home (eg, gas, electric or wood burning stove) and car ownership. During the study period, participants will complete daily diary cards of their symptoms, any changes to their treatment (eg, medications) and sleep disturbance. They will be asked to record their peak expiratory flow on the diary card using a peak flow meter. Spirometry readings will be collected at the initial appointment and subsequent follow-up visits if the participant consents. This will provide information on the severity of their condition and may control for possible random differences.

If at any stage the wearing compliance of the PAM is low, or the participant chooses to withdraw, a replacement will be recruited. Throughout the monitoring period, participants will receive phone calls from the research assistant to check how they are coping with the study. Six weeks into the monitoring period, participants will be invited to attend a clinic with the research assistant to discuss any issues with the PAMs or diary cards. At the end of the monitoring period (at 6 months or earlier if the participant wishes to withdraw), participants will be invited to a final appointment to return the PAMs and completed diary cards.

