### Statistical analysis

Survival analyses for repeated measurements will be performed on the basis of the Cox proportional hazards model. Interval censoring for handing ties over appropriate event time intervals will be applied specifying each participant to a stratum. Essentially, conditional regression will be used to estimate the HR of subjective health symptoms and exacerbations in relation to seasonal variations of personal exposure (prognostic factor). The conditional regression models will be developed by the PHREG procedure in SAS V.9.3 (North Carolina, USA) with robust sandwich covariance for aggregated data. Ties will be handled with the DISCRETE method. Medication use will be inserted as a control factor in the models.

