### Development of a COPD prediction model

Associations between exacerbations with spatiotemporally resolved environmental exposure established in the Statistical associations between personal exposure with COPD-related health outcomes section will be combined with the time-activity exposure model (LHEM) to create a predictive model for COPD exacerbations across London. First, time-location-activity patterns of the COPD cohort will be compared with general population-level time-activity patterns derived from the Traffic Pollution and Health in London project.^24^ This will be used to test the applicability of general population behaviour patterns when assessing COPD associations in epidemiological studies.

The association between personal exposure to air pollution with COPD exacerbations estimated in the Statistical associations between personal exposure with COPD-related health outcomes section will form the basis of the COPD prediction model. This model will be used to create high resolution (20×20 m grid) daily COPD exacerbation risk maps for the years 2005–2011, based on modelled meteorological and pollutant conditions, coupled with typical patient with COPD time-activity patterns identified in the Activity algorithms section. The model will thus retrospectively predict days and locations more likely to trigger a worsening of symptoms and/or exacerbation in patients with COPD over this time period.

The performance of the predictive model will be evaluated using validated methods for patient identification^21^ from EHRs, CPRD, HES and ONS death data excluding data from the COPE cohort. Spatial and temporal patterns of recorded exacerbations will be compared with model risk estimates linked to the home address. If it is demonstrated that there are significant associations between model predictions and recorded exacerbations, the algorithms used will be generalised for use outside of London. These algorithms will provide an opportunity for the development of a national COPD forecasting service with proven performance in predicting increased risk of exacerbations.

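### With participant strata and DISCRETE ties, the planned HR for daily symptoms is in fact a within-person odds ratio; exacerbations are hardly affected

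*Protocol article*

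**What the plan says.** The Statistical analysis section of the protocol article opens with "Survival analyses for repeated measurements will be performed on the basis of the Cox proportional hazards model". On strata it says: "Interval censoring for handing ties over appropriate event time intervals will be applied specifying each participant to a stratum". It then sums up the approach: "Essentially, conditional regression will be used to estimate the HR of subjective health symptoms and exacerbations", in relation to personal exposure. PHREG is the named procedure, with a robust sandwich covariance, and the tie rule is explicit: "Ties will be handled with the DISCRETE method".

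Two other places bear on the point. Under Monitoring phase, "participants will complete daily diary cards of their symptoms", so symptoms are a repeated daily outcome. Under Recruitment of panel participants, the power statement is expressed as a relative risk (about 1.65 for the highest 20% of days, 2.00 for the highest 10%, with 200 exacerbations). It adds: "Other more common outcomes and in particular peak flow will have power to detect smaller associations". The article nowhere calls the estimate an odds ratio, and it gives no daily symptom frequency.

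**The concern.** The procedure, the stratum, the tie method and the effect measure are all fixed in the article, and the first three do not deliver the fourth when days are the unit and events repeat. DISCRETE replaces the proportional hazards likelihood by a discrete logistic one. Within a participant's stratum this is conditional logistic regression, and the exponentiated coefficient is an odds ratio.

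For a rare daily event, the OR, RR and HR coincide for practical purposes. For a symptom present on a sizeable share of days they do not: the OR is further from 1 than the other two, in either direction. Symptom results reported as HRs would then look stronger than they are, and would not be on the same scale as the exacerbation results beside them or the RR used for power.

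**Working it through.** **Inputs from the article.** 160 participants; at least 200 exacerbations; follow-up of up to 6 months (180 days used here); p<0.05 and 80% power (two-sided assumed, as sidedness is not stated); RR 1.65 for the highest 20% of days and RR 2.00 for the highest 10%. **Assumed:** the share of days with a symptom.

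**1. The article's own power figure.** With the usual event formula, events = (1.960 + 0.842)² / [p(1 − p)(ln RR)²].
- p = 0.20, RR = 1.65: 7.849 / (0.16 × 0.2508) = 196 events. With 200 events the minimum detectable RR is exp(2.802/√32) = 1.64, which reproduces the article.
- p = 0.10, RR = 2.00: 7.849 / (0.09 × 0.4805) = 182 events. With 200 events the minimum detectable RR is exp(2.802/√18) = 1.94, so the stated 2.00 is slightly conservative.

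The power figure is sound and is on the RR scale.

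**2. What DISCRETE estimates.** Suppose participant i has D days, of which k are event-days, and a of those k have high exposure. The DISCRETE contribution is exp(βa) divided by the sum of exp(βa_S) over all sets S of k days out of D. The same expression results from logit P(event on day d) = α_i + βx_d after conditioning on k. So β is a log odds ratio. With k = 1 the expression equals the ordinary Cox term; the departure needs several tied event-days in a stratum.

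**3. Exacerbations.** Frequency: 200 / (160 × 180) = 0.69% of person-days, and 200/160 = 1.25 per participant. With RR 1.65 on 20% of days, p0 = 0.0069/1.13 = 0.0061 and p1 = 0.0101. This gives OR = [p1/(1 − p1)] / [p0/(1 − p0)] = 1.657 and grouped-time HR = ln(1 − p1)/ln(1 − p0) = 1.653. The difference is negligible.

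**4. Symptoms: an OR of 1.65 read as other measures.** RR = OR / (1 − p0 + p0·OR), p1 = RR·p0, and HR as above.

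| Assumed baseline p0 | RR | HR |
|---|---|---|
| 10% | 1.65/1.065 = 1.55 | 1.60 |
| 20% | 1.65/1.13 = 1.46 | 1.55 |
| 40% | 1.65/1.26 = 1.31 | 1.45 |

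For a weaker association, OR 1.10, the RRs at the same baselines are 1.10/1.01 = 1.09, 1.10/1.02 = 1.08 and 1.10/1.04 = 1.06.

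**5. Simulation in the other direction.** 160 participants × 180 days, 36 high-exposure days each, true RR 1.65, baseline risk varying between participants, 100 replicates. The same data were fitted with participant strata under DISCRETE and under Breslow ties.

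| Assumed overall frequency | OR by formula | HR by formula | DISCRETE, simulated | Breslow, simulated |
|---|---|---|---|---|
| 0.69% | 1.66 | 1.65 | 1.63 | 1.62 |
| 10% | 1.76 | 1.70 | 1.77 | 1.65 |
| 20% | 1.92 | 1.77 | 1.97 | 1.65 |
| 40% | 2.56 | 2.01 | 2.75 | 1.65 |

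Breslow stays near the true RR at every frequency, so the shift comes from the tie method. The formula uses one common baseline risk, whereas baseline risk varied in the simulation. That is consistent with the simulated DISCRETE values lying above the formula at high frequencies.

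**The case against.** The strongest reply has four parts.

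First, the size is assumed. The article gives no symptom frequency, does not say whether the outcome is any symptom or onset of worsening, and does not fix the event time intervals. A condensed article may leave these to the full protocol. If the outcome is an uncommon onset, the gap is small. The OR of 1.65 is also borrowed from the exacerbation power statement, and the article expects smaller detectable associations for commoner outcomes; at OR 1.10 the absolute gap is only a few hundredths. All of this stands, so the figures are illustrations.

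Second, a reader might infer that symptom odds ratios would distort the London risk maps, because that model is said to "predict days and locations more likely to trigger a worsening of symptoms and/or exacerbation". The documents do not support this. The prediction model section builds the maps on the exacerbation associations; the quoted phrase describes what flagged days may bring about, not what enters the model.

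Third, a reader might infer that a Cox model with one participant per stratum carries no information on exposure, so that the set-up can only be conditional logistic regression. That holds for a single follow-up clock. The article does not specify one, and on a gap-time scale a stratum can hold several spells of the same person. With one event per risk set, DISCRETE equals the Cox likelihood and HR is a fair label. However, the article plans explicitly for ties and records symptoms daily, which is the situation where the two part.

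Fourth, the article already describes the approach as conditional regression. It does, but it still names the result an HR.

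**Conclusion.** The stated effect measure is wrong where a participant's days are compared within the stratum and event-days are tied: the estimate is a conditional odds ratio. The conclusion rests on that day-level reading of the Statistical analysis section, and it matters only for common outcomes, in practice the diary symptoms. For exacerbations the OR, RR and HR agree to within 0.01 (1.657, 1.65 and 1.653).

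For symptoms the size cannot be fixed from the documents. Under assumed baselines of 10% to 40% of days, an OR of 1.65 stands for an RR of 1.55 down to 1.31. For a protective exposure the OR would lie too far below 1, so the accurate statement is that the association is overstated, not that risk is. It would be going too far to conclude that the analysis is invalid: the odds ratio is a legitimate estimate and its test stands. This is an error of naming and interpretation, worth correcting before symptom results are reported.

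**What to change.** State the model as day-level conditional logistic regression stratified by participant, and report conditional odds ratios. For exacerbations, add that these approximate relative risks because the daily event is rare.

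For common daily symptoms, choose one of two routes. Either estimate RRs directly with Poisson regression conditional on participant and participant-clustered robust variance, or keep the planned model and label the symptom results as ORs. In the second case do not convert them to RRs with a single pooled baseline risk. The conditional likelihood does not estimate each participant's baseline, that baseline varies between people, and participants with symptoms on every day or on none contribute nothing to the estimate. If an untied gap-time layout is what is meant, say so; the HR label could then stay for that analysis.

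The cost is a change of wording and a small amount of extra analysis on the same data. Data collection, sample size and the exacerbation-based risk maps are unaffected.

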### Use of EHR to analyse exacerbations

CPRD GOLD data sets will be used to identify general practitioner-treated COPD exacerbations. Information from Hospital Episode Statistics (HES) and the Office of National Statistics (ONS) will also be gathered from CPRD including: accident and emergency admissions, hospital admissions and mortality. Mortality data from ONS will be used as a severity index for exacerbation. Figure 3 shows the covariates and comorbidities to be used in the statistical analysis of COPD exacerbations. Spatial and temporal patterns of recorded exacerbations extracted from historical CPRD, HES and ONS records will be compared with model risk estimates, with the aim of deriving predictive algorithms for future hospitalisations.

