## Discussion

Several studies have attempted to identify relationships between environmental factors and COPD exacerbations.^25^
^26^ However, limitations of the methodological design of previous studies have made it difficult to identify clear links between exposure and health outcomes.

The strength of this study lies in the fact that we will have the ability to assess these associations in far more detail, initially at the individual patient level and potentially at a national level.

For the first time, this study will provide a multidisciplinary methodological framework that will bring together recent advancements in low-cost wearable sensors, computational techniques for the estimation of activity-weighted personal exposure and advanced spatial mapping in a well-characterised population study. The integrated database of environmental stressors and activity patterns at the individual level will form the basis for the validation of the LHEM. The LHEM can further incorporate spatial and temporal patterns of recorded exacerbations extracted from historical CPRD, HES and ONS records to form a COPD prediction model for future hospitalisations.

Limitations include the fact that participants will be asked to participate in the study for up to 6 months in order to try and capture seasonal changes in exacerbations and some may be dissuaded by this. Despite the process of identifying and recruiting patients via CPRD, there may be insufficient numbers of patients who are interested in participating to power the study. Owing to these recruitment concerns, we are not planning to request blood and sputum samples from all participants, and this means that we will not have any biological data from some participants to assess physiological and inflammatory changes during their exacerbations. However, funding has been obtained for a substudy within COPE to collect blood and sputum samples in a subset of 20 participants at baseline, exacerbation and 4 weeks post exacerbation.

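### The only severity index named for exacerbations is ONS mortality, which cannot grade the episodes that patients survive, although the GP, A&E and admission data that could are already being collected

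*Protocol article*

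**What the plan says.** The section *Use of EHR to analyse exacerbations* sets out the data sources: "CPRD GOLD data sets will be used to identify general practitioner-treated COPD exacerbations". From HES and ONS it adds "accident and emergency admissions, hospital admissions and mortality". It then says how severity will be indexed: "Mortality data from ONS will be used as a severity index for exacerbation". The same section compares recorded exacerbations with model risk estimates, "with the aim of deriving predictive algorithms for future hospitalisations". The *Discussion* repeats that goal: "to form a COPD prediction model for future hospitalisations".

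The section *Development of a COPD prediction model* describes a broader target. The model is to "retrospectively predict days and locations more likely to trigger a worsening of symptoms and/or exacerbation in patients with COPD". It is to be evaluated against "EHRs, CPRD, HES and ONS death data excluding data from the COPE cohort".

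No sentence in the text shown grades an exacerbation by where it was treated. *Monitoring phase* speaks of severity only for the underlying condition, through spirometry. Figure 3 is not shown; its caption describes covariates and comorbidities.

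**The concern.** A severity index should rank episodes. Death does not: a patient can die once, and the result is yes or no. An exacerbation managed by the GP and one that led to an emergency admission fall in the same class if both patients survived. Exacerbations also recur, and the Cox model makes each participant a stratum. Within a patient, death can be attached to one episode at most and cannot rank the others.

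Environmental exposure may act differently on mild and severe exacerbations. With nearly all events in one class, that question cannot be examined. It bears on the stated goal as well: the prediction model rests on exacerbations of any kind, yet it is described as a model for hospitalisations. Without a grade that separates admitted from GP-treated episodes, the article gives no stated basis for showing how far the model's performance carries over to admissions.

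**Working it through.** **Inputs from the article**
- *Recruitment of panel participants*: "we will capture at least 200 exacerbations with a cohort of 160 patients"; p<0.05, 80% power; detectable relative risk (RR) about 1.65 for the highest 20% of days and 2.00 for the highest 10%.
- *Monitoring phase*: up to 6 months.

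**Assumptions, not in the article**
- Annual all-cause mortality 2% to 15%.
- Fatality per exacerbation 0.5% to 5%.
- 10% to 20% of exacerbations admitted.
- Two-sided test (the article does not state sidedness).

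**Step 1: the article's own figure.** Schoenfeld's formula, with p the share of high-exposure days:

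events D = (1.960 + 0.842)² / [p(1−p)(ln RR)²]

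- RR 1.65, p = 0.20: 7.849 / (0.16 × 0.2508) = 196 events, against 200 stated. With 200 events, power is 80.9% and the minimum detectable RR is exp(2.802/√(200 × 0.16)) = 1.64. The stated 1.65 reproduces.
- RR 2.00, p = 0.10: 7.849 / (0.09 × 0.4805) = 182 events. With 200 events the minimum detectable RR is 1.94, so 2.00 is a slightly conservative rounding.

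Neither calculation involves the severity index.

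**Step 2: how many exacerbations the index would set apart in the cohort.** Deaths in 6 months = 160 × [1 − (1 − m)^0.5], with m the annual mortality and each death attached to one exacerbation.

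| Assumed m | Deaths | Share of 200 exacerbations | Remaining in one class |
|---|---|---|---|
| 2% | 1.6 | 0.8% | 99.2% |
| 5% | 4.1 | 2.0% | 98.0% |
| 10% | 8.2 | 4.1% | 95.9% |
| 15% | 12.5 | 6.2% | 93.8% |

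The shares are upper limits, because not every death follows an exacerbation. Working from fatality per exacerbation instead, 0.5% to 5% of 200 gives 1 to 10 fatal episodes. An analysis of those alone would have about 4% to 9% power for RR 1.65 (highest 20% of days). The formula is rough at such counts, but the conclusion is not sensitive to that.

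**Step 3: what a grade by level of care would separate.** If 10% to 20% of 200 exacerbations are admitted, that is 20 to 40 events. Minimum detectable RR for the highest 20% of days:
- 20 events: exp(2.802/√(20 × 0.16)) = 4.8
- 40 events: exp(2.802/√(40 × 0.16)) = 3.0

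This separates more events than mortality does, but is still far from the 1.65 available with all 200.

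**Step 4: the historical records.** The counts above do not apply there, since deaths may be a small share yet large in number. The structural problem remains: more deaths do not divide the survived episodes into GP-treated and admitted.

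**The case against.** The strongest reply is that the article calls mortality a severity index and does not say it is the only one. The sentence follows directly on a list of GP-treated events, A&E attendances and admissions, which is the natural ladder of care. Mortality may be meant as its top rung, and the time window and cause coding are details that a journal article may leave to a fuller document. Part of this stands: the data for a better grade are in hand, and the absence of a window or cause rule is no finding by itself. But the article does make a choice here, and the one index it names cannot grade non-fatal episodes.

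A reader might infer three stronger points that the article does not support:
- **That the plan cannot identify hospitalisations.** It can. Admissions come directly from HES and do not pass through the severity index.
- **That hospitalisation goes untested.** HES data are among the records used to evaluate the model. What is lacking is a stated separate result for admissions.
- **That deaths will be only a handful.** That rests on assumed mortality and applies to 160 patients over 6 months. It need not hold in the historical records, and the article does not say that linkage for the cohort stops at 6 months.

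It is also fair to say that the article describes no severity-stratified model, and that grading by level of care would give imprecise estimates in the cohort (Step 3). Both points limit how much is at stake.

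**Conclusion.** The point holds as a badly chosen severity index. By its nature mortality puts every survived exacerbation in one class; this needs no outside figure. For the cohort, about 94% to 99% of the 200 planned exacerbations would share that class. That range rests on assumed annual mortality of 2% to 15%, 6 months of follow-up and one exacerbation per death. In the historical records the number of deaths is unknown, but the index still does not distinguish GP-treated from admitted episodes, so it serves the hospitalisation aim poorly.

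The effect is confined to the grading of severity and to how far the hospitalisation claim can be supported. The sample-size statement reproduces without the index, and the Cox model in *Statistical analysis* does not use it. The point should be addressed, but it does not threaten the main analysis.

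**What to change.** In *Use of EHR to analyse exacerbations*, replace the sentence on ONS mortality with a grade assigned to each episode from the data already listed:
1. GP-treated only
2. A&E attendance without admission
3. Hospital admission
4. Fatal, with a respiratory cause on the ONS record and death within a prespecified window of that episode

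Mortality then serves only for the fourth grade.

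In *Development of a COPD prediction model*, report the validation separately for GP-treated and admitted events, and let the claim about future hospitalisations rest on the admission-specific result.

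The cost is wording and some analysis time; CPRD, HES and ONS data are already planned. The drawback is a small admitted class in the cohort, with a detectable RR of only about 4.8 to 3.0 for an assumed 20 to 40 events. Severity-specific estimates from the cohort should therefore be labelled exploratory.

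### The protocol does not settle whether the historical CPRD/HES/ONS records help derive the prediction algorithms or only test them, so it is unclear whether the test that releases the model is independent

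*Protocol article*

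**What the plan says.** Three sections of the protocol article describe what the historical records are for.

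- **Development of a COPD prediction model.** The cohort's exposure–exacerbation associations are the basis of the model and are combined with the London Hybrid Exposure Model (LHEM). The model yields daily risk maps for 2005–2011. Then: "The performance of the predictive model will be evaluated using validated methods for patient identification" in EHR, CPRD, HES and ONS death data, with COPE participants left out. The evaluation step reads: "Spatial and temporal patterns of recorded exacerbations will be compared with model risk estimates linked to the home address". If significant associations are found, the algorithms are extended beyond London, with a national forecasting service in view.
- **Use of EHR to analyse exacerbations.** Spatial and temporal patterns of exacerbations from the historical records "will be compared with model risk estimates, with the aim of deriving predictive algorithms for future hospitalisations".
- **Discussion.** The LHEM can take in the patterns of "recorded exacerbations extracted from historical CPRD, HES and ONS records to form a COPD prediction model for future hospitalisations".

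None of the three says whether the algorithm is fixed before the historical records are examined, or whether part of the records is kept back.

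**The concern.** The first two sections describe one comparison in nearly the same words: recorded exacerbations against model risk estimates. One section calls it an evaluation. The other gives its aim as deriving the algorithms, and the Discussion points the same way. Leaving out the COPE cohort separates the cohort from the records. It does not separate records used for derivation from records used for testing, if both uses occur.

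The comparison is the release gate. A significant result leads to use outside London, to a claim of demonstrated predictive performance, and, under Ethics and dissemination, to a validated national system offered to healthcare providers. Whether that validation is independent depends on which section governs. A person writing the analysis plan could not tell from the article whether tuning on these records is allowed.

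**Working it through.** **The plan's own figure.** The protocol states no error rate or power for the release test. Its one power statement, under Recruitment of panel participants, is a "minimum detectable relative risk (RR) to detect associations at p<0.05 with 80% power" and concerns the cohort. With 200 events and a two-sided 5% level, the Schoenfeld form gives minimum RR = exp[(1.960 + 0.842)/√(200·p·(1−p))].

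- Highest 20% of days: exp(2.802/√32) = 1.64, against 1.65 stated.
- Highest 10% of days: exp(2.802/√18) = 1.94, against 2.00 stated, which is slightly conservative.

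The figure reproduces, and this point does not affect it.

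**Inputs for the release test.** A two-sided 5% level is assumed, because the protocol says only that associations must be significant. The number of terms or candidates shaped by the historical records, k, is not in the documents and is varied. The list of explanatory variables under Statistical associations between personal exposure with COPD-related health outcomes is long, but it concerns the cohort data and does not fix k.

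**Null pass rate, by how the score was obtained**

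1. *Score fixed beforehand on the cohort and LHEM, then tested on the records.* The rate is the nominal 5%. This is the account under Development of a COPD prediction model.
2. *Best of k independent candidates, chosen and tested on the same records.* The rate is 1 − 0.95^k.
3. *k coefficients fitted jointly on the records, and the resulting score tested there with one degree of freedom.* The score carries the whole k-degree-of-freedom fit, so the rate is P(χ²_k > 3.84).

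| k | Best of k | Joint fit of k |
|---|---|---|
| 1 | 5% | 5% |
| 3 | not used | 28% |
| 5 | 22.6% | 57% |
| 10 | 40.1% | 95% |
| 20 | 64.2% | about 100% |

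The k = 1 row shows the limit of the point. Rescaling a single pre-fixed score on the records leaves a two-sided test at 5%. Inflation starts when there is more than one fitted term or a choice among candidates.

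**Simulation checks, with no true association**

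- 500 observations, 2,000 runs, k = 5, 10, 20: best-of-k passed in 23.6%, 39.6% and 65.6%; joint fit passed in 58.6%, 95.9% and 100%. On fresh data the pass rate was 4.3% to 5.1%.
- 2,556 days (the length of 2005–2011), an assumed Poisson mean of 20 events a day, 1,000 data sets, joint fit of k = 3, 5, 10: 27.9%, 59.8% and 95.0% in-sample. Fitting on the first 1,461 days and testing on the last 1,095 gave 4.8%, 4.9% and 4.2%.

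The arithmetic shows what double use would do. It does not show that double use is planned.

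**The case against.** A reader might infer that the same records certainly derive and test the model, so that the release test is bound to pass far too often. The documents do not support that.

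- The section that specifies the model takes the cohort associations as its basis and tests it in non-cohort records. Read alone, that is external validation at 5%.
- Under Use of EHR to analyse exacerbations, the records are compared with risk estimates, so a model already exists at that point. The stated aim may be the end purpose rather than a fitting step. No tuning, weighting or recalibration is named.
- The Discussion says what the LHEM can take in. That is a statement of capability, not a scheduled analysis.
- Details of a hold-out are what a condensed article commonly leaves to the full protocol or analysis plan. The lack of a stated split is therefore no fault in itself.
- The larger percentages assume joint refitting followed by a naive test. Choosing the best candidate inflates less, and correlated candidates would inflate less again.

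All of this stands against the stronger claim. It does not remove the conflict: a cohort basis does not exclude later adjustment on the records, and two sections use derivation language for data that a third reserves for evaluation.

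**Conclusion.** The finding is a contradiction about the role of the historical records, not established double use. If the model-development section governs, the release test is independent and its null pass rate is 5%. If the derivation wording elsewhere is carried out on the same records, the test is in-sample, and under the assumed k the rate runs from about 23% (best of 5) to 95% (joint refit of 10) and beyond. These figures rest on the assumed k, a two-sided 5% level and, for best-of-k, independent candidates. The documents do not allow one value to be chosen. The direction, and the return to about 5% on untouched data, do not depend on k. The matter should be settled before the records are examined, because an untouched test set cannot be recovered afterwards.

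**What to change.** Reconcile Use of EHR to analyse exacerbations, Development of a COPD prediction model, and the Discussion by stating whether anything in the algorithm is chosen or estimated from the historical records. Then take one of two routes.

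- **(a) Records for evaluation only.** State that the algorithm is frozen on the cohort data and the LHEM before the historical records are examined. Remove the derivation wording from the EHR section and the Discussion. The cost is wording only.
- **(b) Records also used for derivation or recalibration.** Confine that use to a stated subset, for example the earlier years (2005–2008) or a random half of practices. Freeze the algorithm, evaluate it once on the remainder (for example 2009–2011), and base the decision to generalise on that result alone. The cost is wording and a smaller evaluation set.
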